## Abstract

**Background:**

Service and frontline personnel are among the occupational groups with the highest rates of workplace aggression. To address the risk of victimization, various preventive measures have been introduced, with body-worn cameras increasingly adopted. However, evidence of their effectiveness remains inconclusive, with existing studies heavily concentrated in U.S. policing contexts, limiting the generalizability of findings across settings. This study aims to strengthen the evidence base through a randomized controlled trial testing the preventive effect of body-worn cameras among ticket inspectors in Denmark.

**Methods:**

The trial will involve approximately 60 inspectors employed by three Danish public transport companies. Randomization will occur at the shift level, yielding approximately 3,000 shifts in total. The main analysis compares wearing a camera versus not wearing a camera, pooling data from all three companies. A secondary analysis, restricted to two companies, additionally tests whether a visible badge notifying passengers of potential recording strengthens any preventive effect. In parallel, field observations of inspection workdays will be conducted to gain in-depth insights into how and why cameras may influence interactions.

**Discussion:**

This study presents a rare randomized controlled trial on the preventive effect of body-worn cameras against workplace aggression outside a U.S. policing context. If the hypothesis of a preventive effect is confirmed, the findings will have direct practical implications for deploying this technology to reduce workplace aggression.

## Introduction

Work-related violence and victimization present significant challenges for society, employers, and workers. Service and frontline personnel, in particular, face a heightened risk of harassment, threats, and violence compared with other occupational groups [1]. Such vulnerability can result in physical, psychosocial and socioeconomic consequences, including absenteeism, reduced work capacity, and impaired mental well-being [2]. In response, substantial political and organizational efforts have been undertaken to mitigate these risks, such as public campaigns, conflict management training, and improved documentation of incidents.

In recent years, body-worn cameras have emerged as a preventive technology to manage difficult face-to-face encounters with citizens, clients, and customers that service and frontline staff face. The number of occupational groups where body-worn cameras have been used or tested is expanding, and includes police officers [3], transit workers [4], prison and probation service staff [5], retail workers [6], ambulance crews [7], and healthcare professionals [8].

Despite this growing interest, empirical evidence on the effectiveness of body-worn cameras remains inconclusive [9]. Prior research indicates that their effects are highly context-dependent—potentially reducing, increasing, or having no impact on work-related victimization. Moreover, most studies have been conducted with U.S. police, whose experiences differ substantially from those of other frontline workers in other national contexts. In sum, there is a clear need to test the preventive effect of body-worn cameras in settings beyond U.S. policing.

The current study protocol outlines a randomized controlled trial of body-worn cameras that seeks to test whether wearing a camera on the uniform reduces victimization risk, using a design that advances the existing literature in several respects. We conduct a large-scale trial to help resolve the ongoing uncertainty over whether body-worn cameras have a robust effect at all. This test is conducted outside the U.S. policing context—specifically with Danish ticket inspectors—to help clarify the literature’s uncertainty regarding the context dependency of effects. Additionally, we incorporate a range of methodological strategies in our trial design that offer advantages over existing studies. Below, we review the current literature and its limitations and, on this basis, present the study protocol developed to address these gaps.

### Randomized controlled trials on body-worn camera effects

The development of body-worn cameras has led to a growing number of international studies examining their impact on frontline staff’s interactions with citizens, particularly in U.S.-based police–public encounters [10,11]. These studies have explored the camera’s effect on police use of force [12], number of arrests [13], citizen complaints [14], and officer exposure to violence [15]. While studies have looked beyond the policing context, these studies have typically not implemented randomized controlled trials to test the effect of cameras among groups such as prison and probation service staff [5] or ambulance crews [7].

Theoretically, cameras are expected to regulate behavior through a “deterrence effect” or “threat mechanism,” in which their presence signals a higher likelihood of apprehension or conviction, thereby encouraging behavioral compliance [16]. Further, cameras are assumed to promote self-awareness and socially desirable behavior, influencing both the person carrying the camera and the citizen [17].

Beyond deterrence and self-awareness, the camera’s effect may also operate through alternative mechanisms, such as perceptions of procedural justice or organizational practices of conflict management. For example, one study found that citizens reported higher perceived procedural justice in encounters with officers carrying a body-worn camera than in those without [18], which in turn could reduce citizen aggression and staff victimization risk. Additionally, attending to alternative pathways is important if cameras increase rather than decrease victimization. Such a finding could suggest that cameras are experienced as instruments of power display, potentially eliciting defensive or resistant responses from citizens and escalating interactions [19,20].

In line with these considerations, intervention studies examining whether cameras have a preventive effect on victimization of police officers present mixed results. Some U.S.-based studies report an increase in assaults on officers wearing cameras [3], while others from the U.S. and Australia find no significant effect of cameras on victimization risks [15,21]. A meta-analysis concludes significant variation in results regarding assaults against officers, suggesting that cameras can have different effects on citizen behavior under different circumstances. However, these contextual heterogeneities have not yet been documented or understood [9], leaving the interpretation of these mixed results unclear.

A rare exception from the U.S.-police context is a study by Ariel and colleagues from England and Wales that examined assaults against transport personnel [4]. Using 33 train stations as the unit of analysis, they reported a substantial reduction in official assault reports, suggesting that body-worn cameras may help prevent workplace victimization. Although noteworthy for its non-police setting, the study has a key limitation that our trial seeks to address: despite efforts to minimize spillover effects from camera-wearing officers to their colleagues without cameras, randomizing only 33 stations is unlikely to achieve a true balance of confounding factors between treatment and comparison groups. To overcome this, our design randomizes at the level of each inspector’s work shifts, rather than by location alone.

This limitation is closely linked to other methodological issues that call into question the validity of the current evidence and that our study seeks to address. Frequently—also in the study by Ariel and colleagues—victimization is measured using officially recorded incidents [see, e.g., 15]. This approach tends to bias findings toward serious and violent incidents, while overlooking the many more subtle and verbal forms of victimization (e.g., offensive remarks, verbal threats) that often go unreported, despite their potential to reduce well-being. Measuring these more subtle and verbal forms of victimization—as we will do with a survey instrument—is crucial, as inspectors are more often exposed to harassment and verbal threats than to physical violence [1]. The use of a survey instrument in our design also offers an advantage over prior work by enabling us to estimate both intention-to-treat and treatment-on-the-treated effects. Specifically, we survey each treated unit to determine whether a ticket inspector actually followed protocol and wore the camera as instructed (intention-to-treat) or not (actual treatment).

A further methodological limitation is that the experimental literature offers few insights into the effect of body-worn cameras on staff’s perceived safety—an outcome that can, and in our study will, be measured using the survey instrument. The few studies that have considered such perceptions report conflicting views on the camera’s potential to enhance safety across employee groups [22–25]. However, this existing research is based on expectations or retrospective assessments rather than real-time experiences of safety while wearing the camera.

A final methodological limitation of the literature concerns the scarcity of studies examining what happens during actual interactions involving cameras. Although deterrence is a dominant explanation, prior research has not directly investigated the in situ mechanisms at work—for example, whether staff behave differently when wearing a camera. As a result, little is known about the situational mechanisms that may come into play when frontline staff introduce technological surveillance tools into their interactions with citizens [26]. We will address this limitation by conducting a field observation study alongside the experimental intervention, with the aim of directly identifying the operative mechanisms underlying the potential deterrent effect of body-worn cameras [27]. This qualitative component ensures attention to how organizational culture—including practices of camera use and conflict management—may influence the camera’s effect. [28,29]. Additionally, the field observations offer the possibility to examine inspectors’ emotional labor and discretion, which previous research has highlighted as influential for inspectors and frontline staff [30].

### Objective

The purpose of this study is to test the protective effect of body-worn cameras among ticket inspectors in Denmark. We extend the existing literature, which has focused predominantly on U.S. police officers, by examining this effect in a different national context and occupational group. We build on the study of transport personnel by Ariel and colleagues [4] and address key limitations of previous research by implementing a more robust randomization design at the shift level, collecting survey data on both victimization and perceived safety, and triangulating with field observations to identify situational mechanisms. Through this design, we address a central question in the literature: whether the implementation of body-worn camera in frontline encounters has a preventive effect, and under which conditions.

## Methods

### Study design

The study takes place in collaboration with three traffic companies operating trains, buses, and trams in Denmark to conduct a randomized controlled trial on the preventive effect of body-worn cameras for ticket inspectors. The study builds upon a now finalized pilot study with one of the three companies, where the feasibility of the study design was evaluated. The present paper describes the protocol for the full-scale study in which the intervention’s effectiveness will be tested, noting how the final protocol was informed by insights from a small-scale feasibility pilot.

### Intervention setting

The inclusion of three Danish traffic companies ensures variation in geography, demographics, and organizational contexts, including differences in vehicle types, inspector roles, tasks, and educational backgrounds. The companies also differ in their prior experience with body-worn cameras: one uses them routinely, another participated in the pilot phase of the current study, and the third has never used them. All three companies have in-vehicle surveillance cameras, although in one company these are no longer operational. In parts of the transport sector, body-worn cameras are met with mixed reactions—some inspectors welcome them as a security measure, while others express concern, particularly about surveillance and potential misuse of recordings by management. While the intervention will be implemented in the same overall manner across the three companies, certain elements will be adapted to account for differences in work practices and organizational structures, as outlined below.

Company 1 is Denmark’s largest train operator, employing approximately 850 inspectors who service regional and long-distance routes, as well as trains in the urban area of Copenhagen. The company implemented body-worn cameras on a voluntary basis in April 2023 and aims to broaden the use of cameras among employees, with 200 cameras distributed prior to the intervention and approximately 200 more deployed at its onset. The company participates in the study with the aim of reducing work-related victimization and giving non-wearers the opportunity to become familiar with wearing a camera in practice. The company already has formal guidelines for camera use that include an expectation to activate the camera in incidents where a conflict with a passenger escalates. Inspectors are not obliged to inform passengers that they are recording in case they think activation can escalate the incident. On each camera, there is a small sticker announcing potential recording. Inspectors who work in trains operating across the country work alone, except during evening shift after 10 pm, when they work in pairs for safety reasons. Inspectors patrolling the urban rail system work in pairs during evening shifts after 8 pm.

Company 2 employs approximately 20 inspectors who work on trains serving regional routes. The company is motivated to participate in the study to obtain evidence on the preventive effect of cameras on workplace victimization, which could inform their decision regarding the potential implementation of cameras. Company 2 took part in the pilot study with a subgroup of inspectors, meaning that inspectors have either worn a camera themselves or know colleagues who have. Since the pilot study, the workforce has been reduced by half following a change in the company’s ownership. Inspectors always work alone.

Company 3 operates buses and trains in multiple regions, as well as trams in Aarhus, the second-largest city in Denmark. The company comprises two subcompanies. One is a security company contracted to conduct inspections on buses and trams; from this subcompany, 18 guards are employed to carry out inspections for Company 3. Employees always work in units of two to three. The other subcompany is a traffic company with four inspectors responsible for local train routes in a region. These inspectors always work alone. Neither subcompany uses body-worn cameras during inspections.

### Participants

#### Inclusion criteria and recruitment.

Eligible participants are inspectors employed by one of the participating companies who inspect tickets on trains, trams, or buses in Denmark. Ticket inspectors are recruited voluntarily through the participating companies. Recruitment takes place via informational meetings, organizational newsletters, and field visits to staff depots where inspectors typically pass during their shifts. In these settings, we present the study design, summarize previous research, and outline the expected effects of cameras—while stressing the importance of an intervention study to determine these effects conclusively. Inspectors are encouraged to participate regardless of their personal views on cameras, ensuring more robust findings that can better inform future practice.

In Company 1, recruitment began on June 25, 2025, with the first written consent obtained on July 8, and with the first employees having entered the trial on August 20. In Company 2, recruitment and obtainment of informed consent began on June 11, with the first employees expected to enter the trial on September 18. In Company 3, recruitment and obtainment of informed consent began on August 28, with the first employees expected to enter the trial on September 20. Recruitment across the three companies will run until September 30 and the trial will conclude by December 31, 2025.

Upon recruitment, participants are asked to provide written informed consent to share personal information with the research team, in accordance with the General Data Protection Regulation (GDPR), and to read and sign a participant information sheet to provide written consent to participate in the study. The participant information sheet emphasizes that participation is voluntary and acknowledges that the study may involve some risk. In theory, wearing a camera could increase exposure to aggression, although the study anticipates the opposite—a protective effect. Highlighting this potential risk is especially important for employees of Company 1, who already wear cameras in their daily work but will be required to remove the device during control shifts as part of the experiment. The participant information sheet also provides guidance on wearing and using the camera in a safe and de-escalatory manner. Finally, it informs participants that any criticism or concerns they share with the research team, or their decision to opt out, will be treated confidentially to avoid any repercussions from management. Prior to starting in the trial, each participant is asked either over phone or in person to confirm that they still consent to participate in the study.

### Randomization

#### Camera use.

The study randomizes at the level of inspector shifts. Each inspector is assigned to wear a camera during a randomly selected 50% of their shifts over the study period (treatment) and to work without a camera during the remaining shifts (control). Four hours before each shift, participants receive an automated text message indicating whether they must wear a camera for that shift. If a shift starts before 12 pm, the text message is sent the evening before at 8 pm to avoid contacting participants between 8 pm and 8 am. The treatment message is sent within a time span that allows participants to have time to bring the camera to work while minimizing the risk that participants select routes based on whether they carry the camera or not (as some inspectors have freedom in choosing routes). While this design informs inspectors about their condition assignment in a timely manner, it does not eliminate the risk that inspectors adjust their inspection style and manner of coping with passenger conflicts in anticipation of their assigned condition. To assess this bias, we will examine whether outcomes vary across different notification times, on the assumption that shorter notice leaves less room for anticipatory adjustments.

The block-randomization design guarantees an even 50/50 split between treatment and control shifts for every participating inspector. Compared to the field trial by Ariel and colleagues [4], this approach offers key advantages: it ensures treatment and control observations are independent of inspector- or shift-specific characteristics, removes clustering by inspector, increases statistical power, and makes it more likely that randomization produces genuine *ceteris paribus* conditions [31,32]. Despite these strengths, this design carries a risk of contamination, as the same inspectors alternate between treatment and control shifts and may carry learned behaviors, fatigue effects, or other carry-over biases from one condition to the other [see, e.g., 33].

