#### Moderators.

We include a variety of moderators to explore heterogeneities in the camera’s effect on victimization. One group of moderators is measured in the initial baseline survey and includes the inspector’s gender, age, ethnicity, household status, work experience in the company, BMI, prior victimization, prior sick leave due to victimization, baseline sense of safety, and attitudes toward cameras and management. Another group of moderators includes company, shift start and end time, whether the inspector worked alone or in units for some or most of the shift, camera placement on the uniform, and whether a colleague was wearing a camera. All of these moderators are pre-treatment variables and are voluntarily provided by participants.

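### The check for anticipatory adjustment compares outcomes across notification times, but notice length is fixed by shift start time, so as written it mainly compares times of day

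*Protocol article*

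**What the plan says.** All of this is in the protocol article. Under Randomization, Camera use, the unit is the shift: "The study randomizes at the level of inspector shifts". The default message rule is "Four hours before each shift, participants receive an automated text message indicating whether they must wear a camera for that shift". The exception, made so that nobody is texted between 8 pm and 8 am, is "If a shift starts before 12 pm, the text message is sent the evening before at 8 pm".

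The same paragraph concedes that the timing of the message limits route selection but that "it does not eliminate the risk that inspectors adjust their inspection style and manner of coping with passenger conflicts" once inspectors know their condition. To assess that bias, the authors state that "we will examine whether outcomes vary across different notification times, on the assumption that shorter notice leaves less room for anticipatory adjustments".

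Two other sections bear on time of day. Intervention setting says that Company 1's inspectors on national trains work alone "except during evening shift after 10 pm, when they work in pairs for safety reasons", and that "Inspectors patrolling the urban rail system work in pairs during evening shifts after 8 pm". Moderators allows the camera effect itself to differ by shift timing: "Another group of moderators includes company, shift start and end time".

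**The concern.** A comparison across notice lengths is informative about anticipation only if notice varies for reasons unrelated to the outcome. Here camera assignment is randomised but notice is not. Short notice belongs to afternoon and evening shifts and long notice to morning shifts, so passenger mix, staffing and type of shift change along with notice.

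The quantity named is also not the one that carries the bias. Behaviour changed in response to assignment distorts the camera-minus-control difference. It should show as that difference changing with notice, not as the outcome level changing with notice.

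At stake is the credibility of the one quantitative check that the article names for this bias. The assignment is unblinded and both outcomes are self-reported. A reader could take a null result as reassurance, or a positive one as evidence of bias, and neither reading would be justified.

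**Working it through.** **1. Notice as a function of start time.** The article gives no figure for this check, so there is none to reproduce. With start hour h, the messaging rule is:

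- h ≥ 12: notice = 4
- h < 12: notice = (24 − 20) + h = h + 4

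| Shift start | Notice (h) |
|---|---|
| 04:00 | 8 |
| 06:00 | 10 |
| 08:00 | 12 |
| 10:00 | 14 |
| 11:45 | 15.75 |
| 12:00 and every later start | 4 |

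Given start time, notice has no variation. From noon onward it does not vary at all. Apart from a start at exactly midnight (also 4 h), all notice longer than 4 h belongs to starts before noon.

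**2. Outcome level versus camera contrast.** Suppose long notice moves the outcome by −a on camera shifts and by +a on control shifts. With a 50/50 split, the mean outcome moves by 0.5(−a) + 0.5(+a) = 0, while the camera-minus-control difference moves by −2a. A comparison of outcome levels would miss that bias entirely.

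**3. Illustration by simulation.** From the documents: about 3,000 shifts, a 50/50 split and the notice rule. Assumed, to show direction only: starts uniform from 04:00 to 22:00, residual SD 1, camera effect −0.1 SD, a time-of-day trend of 0 or 0.2 SD per 10 h, camera effect changing by 0 or −0.2 SD per 10 h, and anticipation of 0 or −0.2 SD on camera shifts with long notice. There were 1,000 runs per row, ordinary least squares, no clustering and no inspector effects. Entries are the share of runs with p < 0.05.

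| Trend | Camera effect changes with clock time | Anticipation | Outcome by notice | Assignment × notice | Same, adjusted for start time and assignment × start time |
|---|---|---|---|---|---|
| no | no | no | 3.8% | 4.8% | 4.4% |
| yes | no | no | 99.9% | 5.0% | 4.2% |
| yes | yes | no | 68.8% | 67.7% | 6.5% |
| yes | no | yes | 100% | 78.8% | 24.7% |
| yes | yes | yes | 100% | 4.9% | 29.8% |

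- Row 2: a time-of-day trend alone makes the comparison as written flag a bias that is absent.
- Row 3: even the assignment-by-notice interaction is misled if the camera effect varies with clock time. Mean start is 08:00 for long notice and 17:00 for short notice, 9 h apart, so the spurious interaction is 0.2 × 9/10 = 0.18 SD (simulated mean 0.181).
- Row 5: the same variation hides a real effect (unadjusted mean estimate −0.02 against a true −0.20).
- Last column: adjustment for start time leaves the jump at noon to identify the effect. It recovers the assumed value (means −0.19 and −0.20) with a standard error of about 0.144. A 0.2 SD effect is then 0.2/0.144 = 1.39 standard errors, against the 1.96 needed. For 90% power the effect would have to be about (1.96 + 1.28) × 0.144 = 0.47 SD.

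**The case against.** **The notice rule is not useless.** A reader might infer that no analysis under this rule could detect the bias. That goes too far. Notice falls from about 16 h to 4 h at noon, and an analysis built on that drop gives some information, though it is weak and local. Start time is a listed moderator, so no new data are needed. This stands, and the fix uses it.

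**One condensed sentence is not a model.** The article does not exclude a treatment contrast or adjustment for start time, and a full analysis plan may hold more. This stands in part. But the article states both the comparison and the assumption behind it, and that assumption fails for a raw comparison. Reading the sentence as a camera-by-notice contrast does not rescue it without adjustment for start time (row 3).

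**Time-of-day differences are not quantified.** A reader might infer that the check is almost sure to show a difference, or that the companies regard all short-notice shifts as riskier. The documents support neither. They give no victimization rate by time of day. The pairing expressly for safety is one company's late-evening arrangement, whereas the 4-hour group is every start from noon. The 99.9% comes from an assumed trend; without one it is 3.8%.

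**The check is not aimed at route choice.** Correct. The article handles route selection through the message window, and the bias to be assessed is changed inspection style and conflict handling.

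**The consequences are limited.** Also correct. The check enters neither main estimate, and the Discussion openly says that the design does not protect against inspectors adapting to assignment.

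**Conclusion.** The point holds as a flaw in a stated bias check. Notice length is completely determined by start time, so a comparison of outcomes across notification times mainly compares times of day. As written, it can neither show anticipatory bias nor rule it out. That conclusion needs only the messaging rule. The simulation percentages rest on assumed values and show direction, not expected results.

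A reader might go further and infer that the trial's effect estimates are compromised. The documents do not support that: assignment is randomised within inspector and the check feeds into no estimate. What is affected is the interpretation of the results, because a check that does not measure its target could be cited as reassurance.

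**What to change.** Change the analysis only; the messaging rule need not change.

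1. **Replace the comparison.** Regress each outcome on assignment, an indicator of long notice (start before noon) and their interaction. Include start time, assignment-by-start-time and inspector effects, with the cluster-robust standard errors already planned. The interaction is the quantity of interest. It assumes that, notice apart, the outcome and the camera effect vary smoothly with start time through noon.
2. **Report it for what it is:** a low-power check, local to shifts around noon, with its confidence interval and a statement that a null result does not exclude bias.
3. **Add regressions on assignment**, with inspector effects, of recorded shift features that an inspector might alter after the text: shift end time or hours worked, alone or paired, and route only if it is recorded. End time helps only if it is actual rather than scheduled. These regressions detect changed shift selection, not changed inspection style, and should be described that way.

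The cost is slightly more analysis and a less reassuring bias check. Randomising notice within start times would separate the two cleanly, but it is a trade-off. Longer notice on afternoon shifts widens the route-selection window that the article deliberately limits, and it would change messaging in a trial whose first participants entered on August 20, 2025 and which is to conclude by December 31, 2025.
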